### 4.2. Data Management

Personal data collected during the trial will be handled and stored following the General Data Protection Regulation (GDPR) 2018. The use of the study data will be controlled by the principal investigator. All data and documentation related to the trial will be stored in accordance with applicable regulatory requirements, and access to data will be restricted to authorized trial personnel. The trial will be run by principal investigators and co-investigators of the three countries involved.

### 4.3. Dissemination

The dissemination program will involve peer-reviewed scientific journals and national and international conferences. The results will be disseminated to all participants.

## 5. Conclusions

The SAVE system was developed using environmental sensors, smartwatches, smartphones, and a Web application to organize and provide improved service levels to older people, their caregivers, and care organizers. The main functions of the SAVE technology are fall detection, activity level monitoring, heart rate monitoring, door opening detection, water leakage detection, localization, enhanced touch and vocal communication, text messaging, and emergency calls. Data are stored in a cloud-based system that is securely accessible to older care recipients, their caregivers, and care managers.

The cross-national study was designed to evaluate the acceptance, usability, and efficiency of the SAVE system among 165 users of the three types. The exclusion and inclusion criteria for each user type were defined. The planned test environment is the elderly user’s home and the caregivers’ and care organizers’ Web platforms through their applications. The convenient user recruiting method will be applied with the help of retirement clubs and referrals through contacts. Training on using smart devices takes place during the first face-to-face meeting at system installation. The task of the older adult is to wear the watch during the day, put it on the charger at night, and test the alarm and message-receiving functions. Caregivers and care organizers are responsible for reacting to any dispatched notification and regularly opening the SAVE interface, reviewing the information on the interface, and using the information found as possible. The use of a control group is not planned.

The study design follows the mixed method approach where standardized tests and questionnaires, open-ended questions, and log data are collected from the users and the cloud database. The described study design could serve as an inspiring study design framework for similar usability and effectiveness studies.

## Figures and Tables

**Figure 1 ijerph-19-16604-f001:**
[figure not shown]
User account creation.

**Figure 2 ijerph-19-16604-f002:**
[figure not shown]
Aqara Home kit.

**Figure 3 ijerph-19-16604-f003:**
[figure not shown]
Automation sample.

**Figure 4 ijerph-19-16604-f004:**
[figure not shown]
SAVE sensors adapter.

**Figure 5 ijerph-19-16604-f005:**
[figure not shown]
SAVE sensor adapter Wi-Fi setup application.

**Figure 6 ijerph-19-16604-f006:**
[figure not shown]
SAVE configuration app.

**Figure 7 ijerph-19-16604-f007:**
[figure not shown]
SAVE watch face.

**Figure 8 ijerph-19-16604-f008:**
[figure not shown]
Samples of visualization of user data.

**Table 1 ijerph-19-16604-t001:** Eligibility criteria for primary, secondary, and tertiary users.

End User Type	Inclusion Criteria	Exclusion Criteria
Primary users	- Age ≥ 65 years - Mini Mental State Evaluation (MMSE) between 21 and 27 - Healthy or mild to moderate chronic illness or musculoskeletal disease - Feel physically fit to participate in the study (assessment with FAC and Barthel Index): sufficiently capable of moving, able to maintain and change their position, manipulate and move objects, move in their place of residence, experience the surrounding environment, move by means of transport - Live alone - Interest in the project - Willingness to sign the written informed consent - Able to perform the tasks suggested by the caregiver - Able to use smartphone, smartwatch - Presence of a caregiver	- Age < 65 years - MMSE < 21, subjects diagnosed with dementia or with MMSE ≥ 28 or ≤20 - Participants suffer from severe chronic disease (e.g., symptomatic cardiovascular or respiratory disease, myocardial infarction or stroke in the last 6 months, presence of significant visual and/or auditory impairment, severe metabolic dysfunction, oncological pathologies) or severe disability - No agreement on written informed consent - Participants are carriers of cardiac pacemakers or implantable defibrillators - Presence of conditions that make it difficult to use a smart device (e.g., moderate/severe dementia, aphasia, etc.) - A person placed under guardianship - Nickel allergy
Secondary users	- Willingness to sign the written informed consent - Lay caregiver helping the involved older adults (family members, helping volunteers) - Professional assistant to their involved older adults (social worker, nurse, physiotherapist, doctor)	- A person without professional experience in the field of aging care
Tertiary users	- Willingness to sign the written informed consent - Persons who are related to home care and social assistance in municipal care, research field, decision-makers in financing and management	- Less than half a year of experience

**Table 2 ijerph-19-16604-t002:** Dimensions and measures of the evaluation study for all the users.

Type of End Users	Dimensions	Scales	Timing of Data Collection		
			T0	T1	T2
Primary users	Health and Wellness Condition	MMSE	X		
		FAC	X		
		Barthel Index	X		
		SF-12v2	X	X	X
		WHO-5 Index	X	X	X
		EQ-5D-5L	X	X	X
	Self-efficacy	GSE	X	X	X
	Usability and Acceptance	SUS		X	X
		UEQ-S		X	X
		QUEST 2.0		X	X
	Privacy and Stigma	Open questions	X	X	X
Secondary users	Usefulness		X	X	X
	Reliability		X	X	X
Tertiary users	Reduction in time		X	X	X
	Reduction in cost		X	X	X
	Reduction in workload		X	X	X

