## Abstract

Innovative technologies can support older adults with or without disabilities, allowing them to live independently in their environment whilst monitoring their health and safety conditions and thereby reducing the significant burden on caregivers, whether family or professional. This paper discusses the design of a study protocol to evaluate the acceptance, usability, and efficiency of the SAVE system, a custom-developed information technology-based elderly care system. The study will involve older adults (aged 65 or older), professional and lay caregivers, and care service decision-makers representing all types of users in a care service scenario. The SAVE environmental sensors, smartwatches, smartphones, and Web service application will be evaluated in people’s homes situated in Romania, Italy, and Hungary with a total of 165 users of the three types (cares, elderly, and admin). The study design follows the mixed method approach, using standardized tests and questionnaires with open-ended questions and logging all the data for evaluation. The trial is registered to the platform ClinicalTrials.gov with the registration number NCT05626556. This protocol not only guides the participating countries but can be a feasibility protocol suitable for evaluating the usability and quality of similar systems.

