Based on this scenario, eight partners from three countries (Italy, Hungary, and Romania) joined their efforts in the European-funded SAVE (SAfety of elderly people and Vicinity Ensuring) project (EU Grant Agreement AAL-CP-2018-5-149). The SAVE system aims to offer technology-based support to older adults to stay in their familiar surroundings for as long as possible while feeling safe and optimally cared for. The SAVE technology has been designed and developed according to the User Centered Design (UCD) approach, which involves multiple interactions with users to understand their needs and preferences and involve them in the design process for creating a helpful and appreciated technological product [27]. Secondarily, it supports informal caregivers, such as relatives, in providing optimal care for their loved ones while maintaining their professional and private life.

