### 2.3. Participants

The study will involve primary, secondary and tertiary users. According to the European Project SAVE activities, the primary users are expected to be 80 older adults: 30 participants will be enrolled in Romania, 25 in Hungary and the remaining 25 in Italy. Their caregivers (30 participants will be enrolled in Romania, 25 in Hungary and 25 in Italy) as secondary users and at least 5 tertiary users for the site will be enrolled.

Inclusion and exclusion criteria for each end user group are described in Table 1.

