### 2.9. Data Analysis

The proposed study is a small-scale study, carried out as part of an innovation and research project. To calculate sample size, G*Power software (latest ver. 3.1.9.7; Heinrich-Heine-Universität Düsseldorf, Düsseldorf, Germany) [39] was used. The G*Power software supports sample size and power calculation for various statistical methods, including dependent t-test (differences between two dependents means—matched pairs). A power calculation based on a dependent t-test shows that at least 34 end users per group are needed (alpha set at 0.05, beta 0.2 and effect size at 0.5 medium). It will conduct only a partial evaluation of the effectiveness of the services to specific dimensions of the quality of life of the subjects involved. To investigate primary and secondary objectives, the data will be analyzed using qualitative and quantitative methods and mixed analysis methods.

The processing of questionnaire data will be performed through specific software, such as SPSS, Mplus (for the execution of the confirmatory factor analysis), and AMOS (for the execution of the exploratory factor analysis), depending on the needs. The quality of the data and its internal consistency will be evaluated using the Cronbach Alpha and other specific tests. The questionnaires will first be verified manually to check the completeness of the compilation and any apparent inconsistencies. Later, automated routines will be used to detect dubious outliers and records. In such cases, the necessary data cleaning will be carried out.

An Analysis Plan will be defined on the basis of which the analyses themselves will then be conducted. The first step of the analysis will be exploratory in nature. The descriptive analysis of the sample will be conducted through the classic techniques of uni- and bi-variate statistical analysis. Significant differences between outcomes and exposures will be compared using the Chi Quadro test, the Fisher Exact, the t-test, or the Anova test. The characteristics of the subjects will be compared with those of the non-respondents to verify any distortions due to non-responses during the detection.

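### Table 1's only exclusion for secondary users contradicts the inclusion of lay caregivers: as written, a relative or volunteer without professional aging-care experience is ineligible

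*Protocol article*

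**What the plan says.** Table 1 of the protocol article gives eligibility for three user types. For secondary users the inclusion cell asks for willingness to consent and then names two kinds of person. The first is "Lay caregiver helping the involved older adults (family members, helping volunteers"; the second, listed separately, is "Professional assistant to their involved older adults (social worker, nurse, physiotherapist, doctor". The exclusion cell for the same row has one entry: "A person without professional experience in the field of aging care".

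Other parts of the article describe who is meant to take part:

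- The Abstract: "The study will involve older adults (aged 65 or older), professional and lay caregivers, and care service decision-makers".
- The Introduction, on the system's secondary purpose: "it supports informal caregivers, such as relatives, in providing optimal care for their loved ones".
- Section 2.3 on numbers: "Their caregivers (30 participants will be enrolled in Romania, 25 in Hungary and 25 in Italy) as secondary users". It gives no split between lay and professional caregivers.
- Table 1, inclusion of older adults: "Presence of a caregiver".

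Section 2.4 has sites check both the inclusion and the exclusion criteria before the baseline evaluation. Section 2.5 says that data collection began in September 2022.

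**The concern.** The inclusion cell opens the study to relatives and volunteers. The exclusion cell closes it to anyone without professional experience in aging care, which describes the ordinary relative or volunteer. For such a person both rules cannot be followed: enrolment breaches the exclusion, and refusal defeats the inclusion.

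Three things are at stake.

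- **Caregiver ratings.** Table 2 has secondary users rate usefulness and reliability at T0, T1 and T2. If the exclusion is enforced, these ratings come only from people with professional experience and say little about the relatives whom the system is meant to help.
- **Pairing.** Section 2.3 treats secondary users as the caregivers of the enrolled older adults, and section 2.6 links their accounts. An older adult helped only by a relative without professional experience would have no eligible secondary user to pair with.
- **Consistency.** The Discussion says that the study has to run identically in all countries if the data are to be comparable. A rule that contradicts itself leaves each of three countries to choose its own reading.

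**Working it through.** **The plan's own calculated figure.** The only one is in section 2.9: "at least 34 end users per group are needed (alpha set at 0.05, beta 0.2 and effect size at 0.5 medium". It reproduces. For a paired t-test with standardized effect 0.5 and two-sided alpha 0.05, exact noncentral-t power first reaches 0.80 at n = 34 (power 0.808). It contains no caregiver parameter and has no bearing on this point.

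**Applying the two cells together.** The lay and professional entries are read as alternatives, since one person would not normally be both for the same older adult. The rule as written is then:

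eligible = (lay caregiver OR professional assistant) AND consents AND has professional aging-care experience

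| Type of caregiver | Professional aging-care experience | Inclusion cell | Exclusion cell | Result |
|---|---|---|---|---|
| Lay | No | Admits | Rejects | Ineligible |
| Lay | Yes | Admits | Does not apply | Eligible |
| Professional | No | Admits | Rejects | Ineligible |
| Professional | Yes | Admits | Does not apply | Eligible |

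The first row is the contradiction. The third row shows where the exclusion does sensible work: it screens out, say, a nurse or physiotherapist new to aging care.

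**Looking for a passage that limits the exclusion.** The Abstract and Introduction point towards including lay caregivers. Sections 2.3 and 2.4 are silent on the distinction. The Conclusions say only that criteria were defined for each user type. No passage confines the exclusion to professionals.

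**How many people.** Planned caregivers: 30 (Romania) + 25 (Hungary) + 25 (Italy) = 80. Let p be the share who are lay and have no professional aging-care experience. The number ineligible as written is 80 × p. The article gives no value for p, so:

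- p = 0: 80 × 0 = 0
- p = 1: 80 × 1 = 80

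By country the ranges are 0 to 30, 0 to 25 and 0 to 25. The documents do not narrow them.

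**Which outcomes are reached.** Section 2.7 measures the primary outcomes with SUS and UEQ, and the secondary outcomes with WHO-5, EQ-5D-5L and GSE. Table 2 assigns all of these to primary users. Secondary users contribute only the usefulness and reliability items, plus free comments (section 2.8).

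**The case against.** The best defence is that the intent is plain. The inclusion cell spells out family members and volunteers, and the Abstract and Introduction agree. A literal reading would almost empty one of the two categories just named, so the exclusion was probably meant for professional assistants. Nothing shows that any site has used it against relatives. This stands as an account of intent and makes the repair easy. It does not remove the error, because criteria are applied and audited as worded and the wording does not say this.

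The defence is also right to resist several stronger readings that a reader might draw:

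- *That all lay caregivers are shut out.* A relative or volunteer with professional aging-care experience stays eligible.
- *That the main results are compromised.* No outcome in section 2.7 is measured in caregivers, and the sample-size calculation does not use them.
- *That older adults become ineligible.* Their criterion asks that a caregiver be present, not that the caregiver be an eligible, enrolled secondary user. Only pairing is affected.
- *That a majority of caregivers is lost.* Assuming a lay share of 50% to 90%, all without professional experience, gives 80 × 0.5 = 40 to 80 × 0.9 = 72. The documents support neither the share nor the premise that no lay caregiver has such experience.
- *That this wording alone would confound caregiver type with country.* With no quota per site and recruitment through local networks, the mix can differ between countries anyway. Uneven use of the exclusion could add to that.
- *That the absence of a lay/professional variable or of separate reporting is a defect.* The analysis plan and the caregiver sheet are not shown and may already cover it.

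**Conclusion.** The point holds as a contradiction within Table 1, and between Table 1 and the stated aim of involving both lay and professional caregivers. As written, a family member or volunteer without professional aging-care experience cannot be a secondary user. The number affected among the 80 planned caregivers is unknown, between 0 and 80. The contradiction rests on no numerical assumption, only on reading the lay and professional entries as alternatives and on the absence of any limiting text in the article.

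The damage is confined to the caregiver component: who may supply the usefulness and reliability ratings, whether an older adult has an eligible linked caregiver, and whether sites applied the same rule. It should be fixed, but it ranks below faults that reach the primary or secondary outcomes.

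**What to change.** 1. Reconcile the two cells. One way is to open the exclusion entry with a restriction to professional assistants, so that lay caregivers are not judged on professional experience. If the sponsor did intend to require such experience of everyone, the inclusion cell, Abstract and Introduction need to change instead.
2. Notify the ethics committees, as section 4 already provides for protocol modifications.
3. Because data collection is under way, rewording cannot repair screening already done. Before analysis, ask each site how it applied the rule and whether any relative or volunteer was turned away because of it.
4. If any site applied it to lay caregivers, limit the caregiver conclusions there to the kind of caregiver actually enrolled, and say so when comparing countries.

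Recording lay or professional status and reporting the ratings by group would help with step 4, but is an optional extra.

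The cost is one line of eligibility text, one notification to each committee and a short retrospective query to each site. The sample size and the primary and secondary analyses need no change.

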## Data Availability

Not applicable.
